**Figure 1 F1:**
[figure not shown]
**Scheme of the clinical trial visits in the three arms**. V0 = Visit 0; S = Surgery; V1 = Visit 1 (24 hours after surgery); V2 = Visit 2 (72 hours after surgery); V3 = Visit 3 (the day of hospital discharge); V4 = Visit 4 (60 days after hospital discharge). A = Ferric carboximaltose + Erythropoietin; B = Ferric carboximaltose + Placebo; C = Placebo + Placebo

### Study visits

Clinical, analytical and exploratory data needed for the study will be collected by the investigator. Clinical trial visits are structured in five stages as detailed below:

-Visit 0: Screening day.

-Visit 1: In the first 24 hours postoperative period.

-Visit 2: After the first 72 hours postoperative period.

-Visit 3: The day of hospital discharge.

-Visit 4: 60 days at hospital discharge.

### Withdrawal from the study

Each participant will have the right to withdraw from the study at any time. In addition, the investigator may remove a participant from the study at any time if it is considered necessary for any reason including: significant protocol deviation, significant non-compliance with treatment regimen or study requirements, an adverse event which requires discontinuation of the study medication or results, inability to continue to comply with study procedures, consent withdrawn, and loss of follow up.

All the patients leaving the study will fulfill the described procedures of premature finalization as described in the protocol. The analysis will be carried out for all the patients who have received a dose of experimental medicine or control.

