A randomization assignment list will be stratified by center. The randomization list for each center will be sent to the hospital Pharmacy Service at the time of the drug delivery. The person responsible for clinical trials in the Pharmacy Service will be the one responsible for keeping the blinded assignment. The allocation and blinding will be done by masking the syringes of EPO/placebo and iron infusion in the Pharmacy Service of each of the participating centers. The highest quality standards for handling parenteral medications will be kept for the preparation of intravenous mixtures. FC will be performed using plastic bags and opaque infusion sets.

Treatment will be administered in the three arms detailed in Table 2: Erythropoietin + Intravenous ferric carboxymaltose (EPOFE ARM); Placebo of Erythropoietin + Intravenous ferric carboxymaltose (FE ARM); Placebo of Erythropoietin + placebo of intravenous ferric carboxymaltose (PLACEBO ARM). The trial treatment will be administered, regardless of the arm, as soon as possible after inclusion, and always before surgery. Patients will receive the best standard treatment based on protocols existing in each hospital and the best medical care from both the internal medicine and orthopedic teams. Neither intravenous iron nor erythropoietin will be administered to the patient beyond that provided within the clinical trial. All patients could receive complementary oral iron if it is clinically indicated. Additionally, in clinical practice if the hemoglobin at discharge is less than 120 g/L, and no contraindications exits, oral iron regimen will be prescribed to the patient. The promotor's center (Hospital Universitario Virgen del Rocío) will provide the drugs for the trial, experimental and control treatments. The labeling and distribution of the study drugs will be managed by the Pharmacy Service of Virgen del Rocío University Hospital after having obtained the Spanish Regulatory approval for these procedures.

**Table 2 T2:** The three treatment arms of the PAHFRAC-01 clinical trial

TREATMENT ARM	TREATMENT DESCRIPTION
EPOFE ARM	Single dose of 40.000 IU of erythropoietin in a pre-filled 1 ml syringe, subcutaneously. Ferric carboxymaltose 1000 mg (two 500 mg vials diluted in a bottle of 250 ml of saline, in a plastic bag, and with an opaque infusion system), intravenously in a 20-min infusion.

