### Statistical analysis

Both intention to treat (ITT) and per protocol analysis will be performed. The ITT analysis will include all patients who agreed to participate in the study, signed the informed consent, and had been randomized. Per protocol analysis will include the patients who were randomized, received the dose of erythropoietin and ferric carboxymaltose (EPOFE arm), ferric carboxymaltose (FE arm), or placebo (PLACEBO arm), and were operated on; excluding those who discontinued the trial, or received a red-cell pack in a different format than specified in the protocol. Violation of the blinded assignment will be also excluded in the per protocol analysis.

A chi-square test will be performed in order to establish the comparative analysis of the primary efficacy outcome, secondary efficacy, safety and cost endpoints between different arms of the study (Yates correction and, where necessary, Fisher exact test) for qualitative endpoints. Analysis of variance (with post-hoc test of Tukey and T3-Dunette)/Kruskal-Wallis test will be performed for quantitative variables. Differences between groups will be quantified using 95% confidence intervals.

The cost-effectiveness analysis will be performed by incremental cost-effectiveness method, using each patient who did not require RCP transfusion as the primary efficacy unit; each patient surviving at discharge and 60 days after discharge as the high efficiency unit; and the sum of all previously recorded costs of hospitalization as the cost unit. The calculations will be performed as follows: incremental cost-effectiveness (Euros per unit of efficiency gains) = NNT × (cost per a) option patient - cost per b) option patient).

All calculations will be performed using SPSS 18.0. The threshold of statistical significance is set at *p *< 0.05.

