#### Procedures for recording AE

All AEs occurring during the study/or until observed by the investigator or reported by the participant, whether or not attributed to study medication, will be recorded on the CRF. The following information will be recorded: description, date of onset and end date, severity, assessment of relatedness to study medication, other suspect drug or device and action taken. Follow-up information should be provided as necessary.

AEs considered related to the study medication as judged by a medically qualified investigator or the sponsor will be followed until resolution or the event is considered stable. All related AEs that result in a participant's withdrawal from the study or are present at the end of the study, should be followed up until a satisfactory resolution occurs. It will be left to the investigator's clinical judgment whether or not an AE is of sufficient severity to require the participant's removal from treatment. A participant may also voluntarily withdraw from treatment due to what he or she perceives as an intolerable AE. If either of these occurs, the participant must undergo an end of study assessment and be given appropriate care under medical supervision until symptoms cease or the condition becomes stable.

The relationship of AEs to the study medication will be assessed by a medically qualified investigator.

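### The withdrawal rule allows removal from the study, not only from treatment, in a single-dose trial, so outcomes to 60 days after discharge may go uncollected in patients selected by harm or deviation

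*Protocol article*

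**What the plan says.** Under Withdrawal from the study, "the investigator may remove a participant from the study at any time if it is considered necessary for any reason including" a list of grounds that contains significant protocol deviation, significant non-compliance with the treatment regimen or study requirements, and "an adverse event which requires discontinuation of the study medication or results, inability to continue to comply with study procedures". What happens next is given by reference: "All the patients leaving the study will fulfill the described procedures of premature finalization as described in the protocol". The section closes by saying that the analysis covers all patients who received a dose of experimental or control medicine.

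Under Procedures for recording AE, the investigator judges whether an adverse event calls for removal from treatment, and the participant may also withdraw from treatment. Then: "If either of these occurs, the participant must undergo an end of study assessment". On continued follow-up of events, "AEs considered related to the study medication as judged by a medically qualified investigator or the sponsor will be followed until resolution" or stability. Related events that led to withdrawal are also followed to a satisfactory resolution.

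Treatment is brief. Table 2 gives the EPOFE arm "Single dose of 40.000 IU of erythropoietin in a pre-filled 1 ml syringe, subcutaneously" with one 20-minute infusion, and the other arms have the same structure. On timing: "The trial treatment will be administered, regardless of the arm, as soon as possible after inclusion, and always before surgery".

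Outcome measures places the primary transfusion outcome over the hospital stay and the 60 days after discharge, and counts all-cause death at the end of the study. Visit 4, 60 days after discharge, is the only scheduled visit after discharge. Statistical analysis defines the main set: "The ITT analysis will include all patients who agreed to participate in the study, signed the informed consent, and had been randomized".

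**The concern.** The listed grounds suit a trial with repeated dosing, where stopping the drug is a real decision during follow-up. Here the treatment is over before surgery. Apart from an interrupted infusion, or a second component not yet given, there is nothing left to discontinue. Removing a patient later changes no exposure to study drug; all it can end is observation.

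The patients affected are not a random subset. They are picked out by an adverse event or by a deviation, and both may be related to treatment and to later transfusion or death. Outcomes missing for that reason are likely to be informative. Keeping these patients in the intention-to-treat denominator does not supply their outcomes. If one arm has more adverse events and more removals, its deaths would be the ones more likely to go uncounted, and that arm would look safer than it is. Analysis afterwards cannot recover data that were never collected.

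**Working it through.** **1. The two sections side by side.**

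- *Withdrawal from the study:* the action is removal from the study. The decision is the investigator's and is discretionary. What follows is a set of premature-finalization procedures whose content the article does not give.
- *Procedures for recording AE:* the action is removal or withdrawal from treatment. What follows is an end-of-study assessment, with no time stated, and care until symptoms cease or the condition is stable.

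One section ends participation. The other ends treatment but attaches a study-ending step. Neither says that a patient who stops treatment stays in follow-up to Visit 4.

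**2. What is still collected after removal, as far as the article shows.** Related adverse events are followed to resolution. The causality definitions make *related* narrow (no other reasonable cause) and assign events probably due to the patient's clinical state to *not related*. In patients aged 65 or over with a hip fracture, many vascular, cardiac or infectious events could fall in the second class. Following one event to resolution also does not record a later death, transfusion or second event.

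**3. Who is analysed.** The withdrawal section says all dosed patients; Statistical analysis says all randomised patients. These differ for anyone randomised but not dosed.

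**4. The plan's own figures.** Inputs from Sample size calculation: 60% against 40%, one-sided 5%, 80% power, 15% drop-out.

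- Without continuity correction: n = [1.645 × √(2 × 0.5 × 0.5) + 0.842 × √(0.6 × 0.4 + 0.4 × 0.6)]² / 0.20² = 76.2, so 77 per arm.
- With continuity correction: (76.2/4) × [1 + √(1 + 4/(76.2 × 0.20))]² ≈ 86, against 87 stated.
- Inflation: 87/(1 − 0.15) = 102.4, against 102 stated.

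These reproduce closely. The point here disputes none of them, and the fix changes none.

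**5. How far missing outcomes could move the transfusion rate.** Planned drop-out is 0.15 × 102 = 15.3, so about 15 patients per arm have no outcome and 87 do. Assume the 87 run at the planned rates. The lower bound takes none of the 15 as transfused, the upper bound all of them.

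- Placebo: 0.6 × 87 = 52.2. Bounds 52.2/102 = 51% and (52.2 + 15)/102 = 66%.
- Treatment: 0.4 × 87 = 34.8. Bounds 34.8/102 = 34% and (34.8 + 15)/102 = 49%.

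These are extremes and cover drop-out from every cause, of which removal for harm or deviation is an unknown part.

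**6. Direction for death, on assumed inputs.** The documents give neither mortality to 60 days after discharge nor a rate of removal for adverse events. Assume true mortality of 10%, a fraction f of the arm removed (5% to 15%), and mortality q in those removed (20% to 40%), with all of those deaths unrecorded.

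- Among those still followed: (0.10 − f × q)/(1 − f). Mildest case: (0.10 − 0.05 × 0.20)/0.95 = 9.5%. Most severe: (0.10 − 0.15 × 0.40)/0.85 = 4.7%.
- If removed patients were counted as alive: 0.10 − f × q, that is 9.0% to 4.0%.

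This shows the direction only. The size follows from the assumed inputs.

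**The case against.** The strongest reply has five parts.

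- **Discretion.** The investigator may remove a patient; nothing requires it. This stands. The text supports saying that outcomes may go uncollected, not that they are lost.
- **The adverse-event ground is nearly empty.** A reader might infer that a patient with a vascular event two days after surgery would be given the end-of-study assessment then and never reach Visit 4. The documents do not support that. A completed dose cannot require discontinuation, and the adverse-event section sets no time for the assessment. Such a patient could still be removed, but through the open-ended clause allowing any reason, the inability to continue with study procedures, or the deviation and non-compliance grounds. The problem is therefore the breadth of removal from the study, not the adverse-event clause alone.
- **Unseen procedures.** The premature-finalization procedures belong to the full protocol and might include a vital-status or transfusion check. This stands as a limit on the size of the problem. It does not remove the grounds that are stated, or the mismatch between study and treatment.
- **Missing outcomes do not contradict a population definition, and their handling is commonly left to the SAP.** Also fair. The contradiction in the text is narrower: dosed patients in one section, all randomised in the other. The missing outcomes undermine the intention-to-treat analysis without contradicting its definition.
- **Size.** It is tempting to set about 15 drop-outs per arm against the 4 to 8 deaths per arm implied by the 4-8% in the Background (0.04 × 102 = 4.1; 0.08 × 102 = 8.2). That comparison fails: the first is drop-out from any cause, the second in-hospital death only. The trial is double-blind, so unequal removal between arms is possible but not shown.

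**Conclusion.** The point holds as a stated rule that is badly fixed for this design. The article permits ending observation for protocol deviation, non-compliance, an adverse event or any other reason, in a trial whose treatment is finished before surgery and whose transfusion and death outcomes run to 60 days after discharge. It does not reconcile removal from the study with removal from treatment, or the dosed-patient analysis with the all-randomised set.

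The consequence is a risk of informative missing data for transfusion, death, and later or unrelated adverse events. The size of any bias cannot be computed from the documents. The ranges shown rest on the planned all-cause drop-out (51% to 66% placebo and 34% to 49% treatment for transfusion) or on assumed rates (10% true mortality appearing as 9.5% to 4.7%). A reader might go further and conclude that 60-day follow-up of harmed patients is lost, or that a mortality excess in a particular arm would be hidden. The text shows neither, and the procedures for early leavers may reduce the loss.

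**What to change.** In Withdrawal from the study and Procedures for recording AE, define two separate states: no further study treatment, and withdrawal from the study. State that adverse events, non-compliance and protocol deviations do not end follow-up.

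State that vital status, transfusion and adverse events are collected to Visit 4 for every randomised patient, by telephone or record review if needed, unless the patient withdraws consent to follow-up. Make the premature-finalization procedures agree with this.

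Reconcile the withdrawal section's dosed-patient analysis with the all-randomised intention-to-treat set in Statistical analysis.

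The cost is protocol wording and a few more Visit 4 contacts; the visit is already scheduled. Sample size, clinical management and the investigator's discretion over treatment are unchanged.

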### Outcome measures

The primary outcome measure will be the percentage of patients who receive red-cell transfusion during hospitalization, and after 60 days of hospital discharge.

Secondary outcome measures will be the following related with efficacy, safety, HRQoL, and cost-effectiveness

Efficacy end-points: the average number of red-cell packs needed per patient at the end of the study, the average number of red-cell packs needed per patient (only transfused patients), the average hemoglobin level at 24 and 72 hours postoperative period and at hospital discharge, and the total number of hospitalization days.

Safety endpoints: the death rate from all causes at the end of the study; and adverse events including the following clinical complications: vascular events, all kinds of cerebrovascular accidents, acute coronary syndrome, thrombosis, arterial embolism, heart failure, acute/chronic exacerbation of respiratory failure, delirium, thromboembolic disease, catheter-related phlebitis; renal failure; infectious complications: pneumonia, urinary tract infection, surgical-site infection; and all side effects detailed on the EPO and FC data sheet.

HRQoL end-point: Quality of life will be assessed by the Short form 36 version 2 (SF-36) for acute patients [20]. This questionnaire will be administered at inclusion and 60 days after hospital discharge.

Cost-effectiveness end-point: An analysis of incremental cost-effectiveness (using as a primary endpoint each patient not requiring a transfusion, and as a secondary endpoint every patient who survived the index admission) will be performed.

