## Background

Hip fracture (HF) is highly prevalent in Spain, mainly affecting the elderly. It is estimated that 0.7% of women 65 years or older will suffer a hip fracture during their lifetime, and demographic trends predict that the demand for care will double in the next 40 years [1-3]. A total of 4-8% of these patients will die during hospitalization, and fewer than 25% will regain mobility and preserve autonomy at hospital discharge [4,5]. Socioeconomic burden associated to HF is enormous (40.000 euros (57.000 US dollars)) per patient [6].

Anemia is the one of the most frequent complications of HF; around one third to one half of patients will require red-cell pack(s) (RCP) transfusion [7]. RCP transfusion has been the classical choice in treating severe anemia of these patients [7]. Nevertheless, as already stated, the increasing incidence of HF in this population has also raised the need for this valuable and scarce resource. Additionally, RCP transfusions are not without complications [8-11]. In very old and often fragile patients, these effects may involve excess morbidity and mortality, making it necessary to develop blood-saving strategies (BSS) [9,12].

The most important factor in the development of anemia is blood loss, but some other mechanisms (renal failure, inflammation, iatrogenic hemodilution) are also implicated, prompting the choice of different therapeutic approaches [9,13,14]. These rely in three cornerstones: firstly minimizing blood loss in the operating room, secondly rationalizing RCP transfusion protocols, and thirdly enhancing bone-marrow red blood cell production [13-16]. Although evidence that this last measure saves RCP is weak, an increasing number of works have demonstrated notable reductions in RPC transfusion, nosocomial infections, hospital stay, and even survival [14-16]. Nevertheless, some biases in the nature of said studies could partly explain some of the obtained results.

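### As worded, a death before any transfusion counts on the favourable side of the primary endpoint, the primary cost-effectiveness unit and hospital days; the resulting bias is modest and can run either way

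*Protocol article*

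**What the plan says.** Outcome measures in the protocol article defines the primary endpoint: "The primary outcome measure will be the percentage of patients who receive red-cell transfusion during hospitalization, and after 60 days of hospital discharge". The efficacy endpoints in the same section end with "the total number of hospitalization days". All-cause death at the end of the study is a separate safety endpoint. The cost-effectiveness analysis is described as "using as a primary endpoint each patient not requiring a transfusion, and as a secondary endpoint every patient who survived the index admission".

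Statistical analysis puts every consented and randomized patient in the ITT set. It compares qualitative endpoints by chi-square (Yates or Fisher where needed) and quantitative ones by analysis of variance or Kruskal-Wallis. It repeats the effect units, "using each patient who did not require RCP transfusion as the primary efficacy unit; each patient surviving at discharge and 60 days after discharge", and takes "the sum of all previously recorded costs of hospitalization as the cost unit". The incremental ratio is the NNT multiplied by the difference in cost per patient.

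Background gives a mortality figure: "A total of 4-8% of these patients will die during hospitalization". The article shows no rule for how a death enters the transfusion percentage, the length of stay or the primary cost-effectiveness unit.

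**The concern.** Death before transfusion removes the chance of being transfused. Death in hospital ends the stay and can stop costs accruing. Under the stated definitions each of these moves the result in the direction that the trial calls better. An arm with more early deaths would therefore show fewer transfused patients, a shorter stay and a more favourable transfusion-based cost ratio without any effect on the need for blood. An arm with fewer deaths would be penalised, because more of its patients survive to be transfused. Reporting mortality in a separate table does not correct these estimates.

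The setting makes the question relevant. In-hospital mortality is not negligible, treatment is always given before surgery, follow-up runs to 60 days after discharge, and the abstract names mortality in the objective.

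**Working it through.** **Inputs from the article.** Transfusion 60% on placebo and 40% on treatment; one-sided, 95% confidence, 80% power; 87 per arm, 102 after 15% drop-out (Sample size calculation). In-hospital mortality 4-8% (Background).

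**Assumptions, not in the article.** Mortality by arm (4% v 8%, with 4% v 12% as a more extreme case); the share f of deaths early enough to pre-empt a transfusion; need for transfusion independent of death.

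**1. The plan's own figure.** Uncorrected n = [1.645·√(2·0.5·0.5) + 0.842·√(0.24 + 0.24)]² / 0.20² = 76.2. With continuity correction: (76.2/4)·[1 + √(1 + 4/(76.2·0.20))]² = 85.9, so 86 against the stated 87. Then 87/0.85 = 102.35, stated as 102. The sample size is not in error on this point.

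**2. Where an untransfused in-hospital death lands.**
- Primary endpoint, ITT: in the denominator, not transfused (favourable).
- Primary cost-effectiveness unit: a patient without transfusion (favourable).
- Hospital days: truncated stay (favourable).
- Hospitalization costs: can be lower; the article has no cost-by-outcome data.
- Survival cost-effectiveness unit: failure.
- All-cause death: counted as a death.

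**3. Size of the bias with no true effect.** Observed transfusion rate = 0.60 × (1 − m·f), with m the arm's mortality. The false-benefit rate is the chance of a significant result in favour of the higher-mortality arm at 102 per arm, by the normal approximation for two proportions without continuity correction.

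| m, placebo v active | f | Observed rates | Difference | One-sided false-benefit rate (nominal 5%) |
|---|---|---|---|---|
| 4% v 8% | 0.25 | 59.4% v 58.8% | 0.6 | 6.0% |
| 4% v 8% | 0.50 | 58.8% v 57.6% | 1.2 | 7.1% |
| 4% v 8% | 1.00 | 57.6% v 55.2% | 2.4 | 9.7% |
| 4% v 12% | 1.00 | 57.6% v 52.8% | 4.8 | 16.9% |

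With a two-sided test, the benefit tail in the first three rows is 3.1%, 3.7% and 5.3% instead of 2.5%. Exchanging the mortality figures between arms reverses the sign of each difference.

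**4. What f means.** Here f is the share of deaths that come early enough to pre-empt a transfusion. It is not the share of the dead who were untransfused. If f meant the latter, with survivors transfused at 60%, the rate would be 0.60·(1 − m) + m·(1 − f) = 0.60 + m·(0.40 − f). At 4% v 8% this gives:
- f = 0.25: 60.6% v 61.2% (sign reversed)
- f = 0.40: no difference
- f = 0.50: 59.6% v 59.2% (0.4 points)
- f = 1: 57.6% v 55.2% (2.4 points, as above)

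**5. Could deaths alone produce the planned effect?** A 20-point difference needs 0.20/0.60 = 33 points of excess pre-emptive mortality. Bare one-sided significance at 102 per arm (61 v 49 transfused, 12/102 = 11.8 points) needs 11.8/0.60 = about 20 points.

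**6. Would the separate mortality comparison show it?** At 102 per arm, the power to detect 4% v 8% at two-sided p < 0.05 is about 22%.

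**7. A transfused-or-died composite** (death independent of transfusion).
- No effect on transfusion, mortality 4% v 8%: 1 − 0.40·0.96 = 61.6% v 1 − 0.40·0.92 = 63.2%, so the excess deaths count against the arm.
- True 60% v 40%, mortality equal at 4%: 61.6% v 42.4%, one-sided power at 87 per arm 82%.
- True 60% v 40%, mortality equal at 8%: 63.2% v 44.8%, power 79%.
- Present endpoint on the same basis: 84%.

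**The case against.** The strongest objection is scope. This is a condensed article, and the full protocol or the SAP may say how deaths are counted and which sensitivity analyses are run. That is fair, and the absence of such a rule is not the point here. What the article does fix (endpoint, ITT denominator, effect unit, hospital days) puts an early death on the favourable side if followed literally.

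A reader might go further and infer that excess mortality would pass for efficacy. The article does not support that:
- The second cost-effectiveness unit is survival, so a death is a failure there; only the transfusion unit has the problem.
- All-cause death is compared between arms, so a large excess would be visible. This protection is limited, since a doubling from 4% to 8% would usually not reach significance.
- The per-protocol set requires surgery, so deaths before surgery drop out of it. They remain in the ITT analysis.
- Vascular events and death are listed as safety endpoints and complications, not as known effects of the study drugs. The stated hope is lower mortality, in which case the bias runs against treatment.

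The size is also fairly challenged. The 4-8% is a background range for hip-fracture patients, and placing its ends in opposite arms is an assumption. The 12% lies outside that range. Deaths after discharge matter for the primary endpoint only where a first transfusion would still have followed, and the article gives no rate for that.

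**Conclusion.** The point holds in a limited form. Followed as written, the primary endpoint, the primary cost-effectiveness unit and hospital days all favour the arm with more early deaths, in whichever direction mortality differs. At an assumed 4% v 8% mortality, 60% need and no true effect, the primary endpoint shifts by 0.6 to 2.4 points, and the one-sided false-benefit rate rises from 5% to between 6% and 10%. An assumed 4% v 12%, with every death pre-empting a transfusion, gives 4.8 points. Against a 20-point target this adds to, or subtracts from, an apparent benefit but could hardly create it. The shift in hospital days and costs cannot be sized from the article. The figures rest on the assumed mortality by arm, the assumed share of pre-emptive deaths, and independence of death and transfusion need. The planned primary endpoint can stand if supportive analyses that handle death explicitly are reported beside it.

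**What to change.** Keep the primary endpoint and the sample size, state how a death is counted, and pre-specify three additions:

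1. A supportive analysis of transfused or died by 60 days after discharge, with the same test as the primary endpoint.
2. In the Kruskal-Wallis comparison of hospital days, the worst rank for in-hospital deaths, at least as a sensitivity analysis. Days alive and out of hospital is a reasonable alternative.
3. A supplementary cost-effectiveness ratio per patient alive and untransfused, beside the planned transfusion and survival units.

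All three use data already collected, so the cost is a few extra analyses. The downside is that the composite mixes outcomes of different weight, and its power is slightly lower when mortality is equal (82% or 79% against 84% at 87 per arm). It should therefore stay supportive and not replace the primary endpoint.

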### Sample size calculation

Sample size was calculated as follows:

-To obtain statistical significance in the comparison between the i.v. iron + EPO arm compared to placebo. The treatment arm exclusively with iron is only used in the evaluation of results, but not in the sample size calculation.

-To obtain a confidence level of 95% and 80% power.

-To be single sided.

-To obtain a reduction in the primary endpoint of 20% (percentage of patients who need transfusions), which is considered as clinically significant in the literature. According to this, we would expect the percentage of patients who need to be transfused in the placebo group to be 60% and in the treatment group 40%.

-Sample size was calculated online using SISA http://www.quantitativeskills.com/sisa/calculations/samsize.htm. A total of 87 patients per arm are needed with the foregoing conditions.

-Taking into account a percentage of drop-outs of 15% per arm, the total number of patients per arm is set at 87 × (1/1-0.15) = 102, a total of 306 patients.

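### The mean number of packs in transfused patients only is listed as an efficacy end-point, but it conditions on the primary outcome, so its between-arm test is not protected by randomisation and can mislead

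*Protocol article*

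**What the plan says.** The Outcome measures section defines the primary outcome first: "The primary outcome measure will be the percentage of patients who receive red-cell transfusion during hospitalization, and after 60 days of hospital discharge". It then lists two end-points on the volume of blood given, one after the other, both as secondary efficacy end-points. The first covers all patients: "the average number of red-cell packs needed per patient at the end of the study". The second is restricted: "the average number of red-cell packs needed per patient (only transfused patients").

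The Sample size calculation expects the "percentage of patients who need to be transfused in the placebo group to be 60% and in the treatment group 40" per cent.

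The Statistical analysis section gives one rule for continuous and count outcomes: "Analysis of variance (with post-hoc test of Tukey and T3-Dunette)/Kruskal-Wallis test will be performed for quantitative variables". It adds 95% confidence intervals for differences between groups and a significance threshold of p < 0.05. It does not exempt the transfused-only mean, call it descriptive, or say how the selection is to be handled.

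**The concern.** Randomisation makes the arms comparable as randomised. It does not make the transfused patients of one arm comparable with the transfused patients of another, because whether a patient is transfused is decided later and is what the treatment is meant to change. If EPOFE mainly spares patients close to the transfusion threshold, those who are still transfused are on average the heavier cases, while the placebo subset also contains the lighter ones. The difference in means then mixes an effect of treatment with a difference in case mix, and the data on transfused patients alone cannot separate the two.

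At stake is one secondary efficacy result. Tested as the plan stands, it could come out significantly against a treatment that lowers both the proportion transfused and the total blood used. The protocol gives no rule for reading it beside the all-patient mean if the two disagree.

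**Working it through.** **Inputs from the protocol article.** Transfusion rates are 60% (placebo) and 40% (treatment). The planned size is 87 per arm, or 102 after allowing for 15% drop-out, with one-sided 5% significance and 80% power (Sample size calculation). The test is analysis of variance or Kruskal-Wallis at p < 0.05 (Statistical analysis). The protocol gives no distribution of packs per patient, so every pack distribution below is an assumption.

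**The plan's own figure.** With pooled variance and no continuity correction:

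n = [1.645 × √(2 × 0.5 × 0.5) + 0.842 × √(0.24 + 0.24)]² / 0.20² = 76.2, so 77.

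With the continuity correction:

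n = (76.2 / 4) × [1 + √(1 + 4 / (76.2 × 0.20))]² = 85.9, so 86.

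The plan states 87, which agrees within one patient. Then 87 / 0.85 = 102.4, against 102 stated. These figures rest on the binary primary outcome alone, so nothing below affects them.

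**Who enters the restricted comparison.** At 102 per arm: 0.60 × 102 = 61 placebo and 0.40 × 102 = 41 EPOFE patients. At 87 per arm: 52 and 35.

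**Assumed placebo arm, per 100 patients.** 40 receive none, 20 receive 1 pack, 30 receive 2 and 10 receive 3.
- All patients: (20 × 1 + 30 × 2 + 10 × 3) / 100 = 1.10.
- Transfused only: 110 / 60 = 1.83.

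**Three ways for EPOFE to spare 20 of the 60.** In none of them does any patient need more packs than before.
1. Only one-pack patients are spared, leaving 0/30/10. Transfused only: 90 / 40 = 2.25 (+23%). All patients: 90 / 100 = 0.90 (−18%).
2. Half-selective: 10 one-pack patients are spared first, leaving 10/30/10, and the other 10 are spared in proportion (× 40/50), leaving 8/24/8. Transfused only: (8 + 48 + 24) / 40 = 2.00. All patients: 0.80.
3. Proportional: every group × 40/60, leaving 13.3/20/6.7. Transfused only: 73.3 / 40 = 1.83. All patients: 0.73.

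**A model in which everyone's need falls.** If packs are Poisson, the mean is −ln(proportion not transfused). Placebo: −ln 0.40 = 0.916. EPOFE: −ln 0.60 = 0.511. Transfused only: 0.916 / 0.60 = 1.53 against 0.511 / 0.40 = 1.28, which is the right direction.

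**Other assumed placebo splits, lightest needs spared first.**

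| Placebo patients per 100 | Transfused-only mean, placebo | Transfused-only mean, EPOFE |
|---|---|---|
| 25/25/10 at 1/2/3 packs | 1.75 | 2.13 |
| 40/10/10 at 2/3/4 packs | 2.50 | 2.75 |
| 30/20/10 at 1/2/3 packs | 1.67 | 2.00 |

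**How often the test would be significant in the harmful direction.** This was simulated with 4,000 two-arm trials per case, using Kruskal-Wallis among the transfused. In case 1 it happens in about 89% of trials at 87 per arm and 94% at 102. In case 2 it happens in about 20% to 24%. The simulation compares EPOFE with placebo only; the plan's test spans three arms with post-hoc comparisons.

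**The case against.** The strongest reply is that the protocol already contains the sound version. The end-point listed immediately before this one is the mean over all patients. A reader might infer that the trial measures blood volume only in transfused patients; the Outcome measures section shows that this is not so. On a common analysis set the all-patient mean equals the proportion transfused times the transfused-only mean: 0.60 × 1.83 = 1.10 and 0.40 × 2.25 = 0.90. In the worst case shown, a reader would therefore see 60% fall to 40% and 1.10 fall to 0.90 next to the rise from 1.83 to 2.25. That limits the risk to one line of the results. It does not repair that line, which has the same efficacy status and falls under the same test.

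A second reply is that the reversal depends on who is spared, and the documents do not say. This stands. A reader might infer that an effective treatment will look harmful, or that EPOFE necessarily keeps the harder cases. Neither is supported: proportional sparing gives no difference, and a general fall in need gives the right sign.

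A third reply is that the test is inferred from a general sentence on quantitative variables, not stated for this end-point. That is true, but the end-point is quantitative, it is listed under efficacy, and nothing exempts it.

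Finally, packs per transfused patient can be of practical interest. That is a reason to report the figure, not to test it between arms.

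**Conclusion.** The point holds in a limited form. The plan implies a between-arm significance test within a subgroup defined by the primary outcome, and the planned effect itself makes the two subsets unequal (about 61 against 41 per 102). That much follows from the document alone.

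The direction and size of the distortion do not. Under the assumptions shown, the transfused-only mean for an effective treatment ranges from 23% above placebo, through equality, to a difference in the right direction (1.28 against 1.53), while the all-patient mean falls in every case. The end-point can mislead, but need not.

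A reader might go further and infer that the trial's main conclusion is at risk. The document does not support this: the primary outcome, the sample size and the all-patient mean do not depend on this end-point. The change is still worth making, because the test as planned cannot be read causally and is cheap to drop.

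**What to change.** Keep the all-patient mean number of packs, with patients who receive none counted as zero, as the only tested end-point on blood volume. It is already in the protocol, so nothing has to be added. Report the transfused-only mean by arm as a description, without a p-value, beside the percentage transfused, so that readers can see how the all-patient mean is made up. State in the analysis plan that it will not be used as evidence of efficacy or harm.

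The cost is a change of wording and one secondary p-value. No new data or extra patients are needed, and the primary analysis and sample size stay as they are. The model for the all-patient count can be left to the analysis plan; this correction does not depend on it.
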